## **Control Sites**

We will identify usual care control sites to examine temporal trends in outcomes among non-intervention sites. Our plan is to identify 5 to 6 controls for every participating ASAP site, if that is not possible (due to matching constraints), then we will plan to use 4 controls for each ASAP site. For example, we will use administrative data to examine the use of polysomnography across stroke/TIA patients in the VA system and compare changes in matched controls versus our intervention sites on the diagnostic rate. We will employ the same adjustment approach as described above for control sites.

Control sites will be matched to intervention sites on the basis of:

- Cerner status (all intervention sites are using Vista/CPRS)
- Volume of TIA and ischemic stroke patients
- VA Complexity level (all of the intervention sites are Level I; therefore, all control sites will also be Level 1)
- Baseline diagnostic rate

Given that some VAMCs do not provide acute stroke care, we will examine the proportion of stroke/TIA patients who were transferred out of the facility within 2 days of presentation as a measure of how well the sites are matched. If there is imbalance in this measure, we may add it as an explicit matching criterion.

Update: Eligible control sites were restricted to be Level 1 complexity and using Vista/CPRS similar to intervention sites. Sites were then matched on volume of TIA and ischemic stroke patients and baseline diagnostic rate. The transfer rate was compared and was less than 3.5% at all control and intervention sites thus was not used as a matching criterion.

| Table 3. Diagnostic Rate |        | Active vs Control | Sust. vs Control  | Sust. Effect             | Active            | Sust. Effect      | Sust. vs Control         | Active vs Control | Sust. vs Control  | Sust. Effect             |
|--------------------------|--------|-------------------|-------------------|--------------------------|-------------------|-------------------|--------------------------|-------------------|-------------------|--------------------------|
|                          |        | $H_0: \theta = 0$ | $H_0: \gamma = 0$ | $H_0: \gamma = \theta_M$ | $H_0: \theta = 0$ | $H_0: \gamma = 0$ | $H_0: \gamma = \theta_M$ | $H_0: \theta = 0$ | $H_0: \gamma = 0$ | $H_0: \gamma = \theta_M$ |
| Control                  | Active | CV = .3           |                   |                          | CV = .5           |                   |                          | CV = .8           |                   |                          |
| 7%                       | 13%    | 0.77              | 0.14              | 0.27                     | 0.74              | 0.13              | 0.26                     | 0.72              | 0.12              | 0.25                     |
| 7%                       | 13.50% | 0.84              | 0.15              | 0.31                     | 0.81              | 0.14              | 0.29                     | 0.79              | 0.13              | 0.28                     |
| 7%                       | 14%    | 0.89              | 0.17              | 0.35                     | 0.86              | 0.16              | 0.33                     | 0.85              | 0.15              | 0.32                     |
| 7%                       | 15%    | 0.95              | 0.21              | 0.44                     | 0.93              | 0.19              | 0.41                     | 0.93              | 0.18              | 0.4                      |

**Power and Sample Size Analysis** We will use randomization to determine the order in which the 6 participating intervention sites will receive the ASAP program. Our primary power analysis is driven by the stepped-wedge design using large-sample theory that site-level sampling proportions are

distributed approximately normal. Based on this assumption, we estimated the statistical power to detect the treatment effect  $\beta$ , while varying the intra-cluster correlation.

### **Diagnostic Rate**

(Power for Diagnostic Rate: Active Implementation versus Baseline)

Using a stepped-wedge with 6 VA sites, 8 total time points, 2 sites switching at each step, and approximately 64 patients per site ( $111 \times 7/12$ ) at each step, we should have over 90% power to detect a difference in diagnostic rate of 7% and 15% while varying the coefficient of variation (or intra-cluster correlation). 7% was the observed diagnostic rate in FY2017, and intervention is expected to increase the diagnostic rate to 70% so we are appropriately powered for this primary outcome. The detectable intervention diagnostic rate is provided in the table based on the two-sided test statistic while varying the coefficient of variation. We additionally ran 1,000 simulations with varying treatment effects, including a large random site-effect  $u_j \sim N(0, \tau^2)$ , with  $\tau^2$  based on ICC (.03, .05, .20), a linear time-effect ( $\gamma = 0.005$ ), and assuming a diagnostic rate in the control phase of 7%. We then fit the proposed linear mixed model with time as a categorical variable. Even in the extreme case that our ICC is large (ICC = 0.2), we are still adequately powered to detect the difference in diagnostic rate of 7% and 15% (Table 3). This initial power calculation was revisited to include additional baseline data and a slight reduced sample size because of the COVID-19 pandemic. The results of the updated power calculation did not differ substantively from the initial (above) power calculation.

**Secondary Analyses Effectiveness** The three secondary effectiveness outcomes are 30-day treatment rate, 90-day recurrent vascular event rate and 90-day all-cause readmission rate.

**30-day Treatment Rate** is defined as PAP treatment initiation within 30 days of presentation to the facility. The mean facility 30-day treatment rate is defined as PAP initiation within 30 days of admission. For this outcome, the denominator will be patients who are newly diagnosed with OSA. Patients with a prior diagnosis of sleep apnea (regardless of CPAP usage) and those who die within 7 days of discharge will be excluded. Patients who have a new diagnosis of central sleep apnea or Cheyne stokes (within 30-days of admission) or who are using Adaptive Servo Ventilation (ASV) are excluded. There may be no (or very few) patients in the baseline phase with OSA who are given treatment. Therefore, we will collapse data across all control time increments and all intervention time increments for each site.

**90-day Recurrent Vascular Event Rate** includes an ED or hospital admission for any of the following: TIA, stroke, myocardial infarction (MI), acute coronary syndrome (ACS), arrhythmia, congestive heart failure (CHF), and all-cause mortality. The recurrent vascular event rate is measured from the day discharge.

Patients who are transferred out from the index stay are excluded. We expect the intervention only to reduce recurrent vascular events among patients with OSA who receive and adhere to treatment.

**90-day All-Cause Readmission Rate** includes an inpatient admission for any cause at either a VA or non-VA acute care facility. Planned readmissions are not included in the numerator. Patients who are transferred out from the index stay are excluded from the denominator. Exclude patients who were transferred to an acute care facility at any time during the index admission. As with the recurrent vascular event rate, we expect the intervention only to reduce readmission among patients who are diagnosed with OSA who receive and adhere to treatment.

**Baseline Characteristics** We expect that the characteristics of the stroke/TIA patients will remain relatively constant at each site across the different time points. We will summarize patient characteristics (e.g., demographics) by site and time. Any differences will be considered when interpreting results of analyses.

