| A                 | 212                                    | 30                 | 18                       | 172                                   |
| B                 | 150                                    | 26                 | 17                       | 111                                   |
| C                 | 169                                    | 52                 | 20                       | 107                                   |
| D                 | 157                                    | 30                 | 23                       | 116                                   |
| E                 | 141                                    | 37                 | 37                       | 92                                    |
| F                 | 172                                    | 39                 | 32                       | 117                                   |
| National average  | 158.2                                  | 37.3               | 25.4                     | 107.5                                 |
| ASAP sites | 157.3                           | 35.2        | 20.3              | 119.2                          |

aAnnual stroke/TIA volume based on FY2017 data and excludes patients with a history of OSA. bPotentially eligible patients exclude those with: history of OSA, PSG in prior 5 years, death within 7-days of discharge, and hospice referral.

**5.1.c. Intervention Description** The quality improvement intervention will include: a systems redesign Virtual Collaborative and data monitoring.

**Systems Redesign Virtual Collaborative** A Virtual Collaborative will be convened among the investigators and the clinical team members from the active implementation sites. The site clinical teams will include members from the stroke team, sleep medicine, and systems redesign. The Virtual Collaborative will be used to develop system redesign approaches to overcome barriers to

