In considering the types of Veterans who would be eligible for sleep apnea diagnostic testing or treatment, we should first note that at all times treating providers (the target of the research) will hold patient safety in the highest regard. Thus, by keeping contraindications to PAP therapy in mind, providers may decide to exclude patients from PAP therapy. This would be the case for Veterans who meet inclusion criteria for the study (i.e., being admitted to an ASAP VAMC with the diagnosis of ischemic stroke or TIA who do not have an existing diagnosis of sleep apnea) but their healthcare provider, in the course of delivering routine clinical care, makes the decision that a given Veteran has a contraindication to PAP therapy. Inclusion criteria would include patients admitted to an ASAP VAMC with the diagnosis of an ischemic stroke/TIA without a prior diagnosis of OSA. Exclusion criteria for Veterans will include being admitted to an ASAP VAMC with a diagnosis other than ischemic stroke or TIA (e.g., syncope, seizure), Veterans not admitted to a VAMC for their acute cerebrovascular care

(e.g., presented to the Emergency Department and transferred to a non-VAMC), or a known history of sleep apnea.

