sparse data for the baseline phase, we plan to collapse data within each site across the baseline phases and the treatment phase and compare the within site treatment rates using a permutation test. Doing so will randomly flip the treatment labels of site-level treatment rates. Because there are 6 sites, there are  $2^6$  possible permutations of the treatment labels within pairs. The p-value will then be the proportion of permutations that lead to a test statistic at least as extreme as the actual data. Additionally, we will report the estimated site-level treatment rate during the baseline and intervention phases as well as the associated 95% CIs. We will also compare the overall treatment rate among all patients in the baseline phase to all patients in the active implementation phase using Fisher's exact test.

**90-day Recurrent Vascular Event Rate and Readmission Analysis** will be analyzed similarly to the primary outcome with the exception that the 7-month code-red data period (beginning 9/2021) will not be included. Models for the secondary outcomes (excluding treatment rate) will be fit without covariates (unadjusted) and additionally including patient-level factors (adjusted).

**Missing Data** Because we are using centralized chart review augmented by data from the CDW to collect our baseline characteristics and outcome data, we expect to have very little missing data. Only a few of the patient-level variables which may be included in the models adjusting for covariates may contain a small amount of missing such as stroke severity (as measured by the NIHSS). The amount of missing will be examined before deciding on the handling of missing data. Either complete-case or multiple-imputation will be used for models adjusting for patient-level factors. In the highly unlikely event that for a certain time period we are not able to get data from a specific site, the mixed effects model allows us to still use data for the other time periods for that site. The proposed mixed model methods are appropriate as long as data are missing completely at random (MCAR) or missing at random (MAR). If for any reason, we suspect the pattern of missing data is non-ignorable, more complex modeling approaches may be used.

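### As written, the 90-day readmission rate counts a patient who dies after discharge without an unplanned readmission as not readmitted, so a mortality difference between phases moves the rate the opposite way

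*Protocol*

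**What the plan says.** All references are to the protocol. The readmission outcome is defined in section 5.7.c, Secondary Analyses Effectiveness:

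- Numerator: it "includes an inpatient admission for any cause at either a VA or non-VA acute care facility", and "Planned readmissions are not included in the numerator".
- Denominator: "Patients who are transferred out from the index stay are excluded from the denominator". A further sentence repeats the transfer exclusion. No other exclusion is given.
- Time origin: none is stated.
- Analysis: the paragraph on the 90-day vascular event and readmission analyses says that these outcomes "will be analyzed similarly to the primary outcome", apart from leaving out the code-red period. The primary outcome is a patient-level yes/no variable in a generalized linear mixed model.

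The two neighbouring outcomes do deal with death. For the treatment rate, "those who die within 7 days of discharge will be excluded". The 90-day vascular event rate ends its list of events with "congestive heart failure (CHF), and all-cause mortality", and its clock starts at discharge.

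Elsewhere, section 5.4 sets the patient-level exclusions: "Exclusion criteria for Veterans will include being admitted to an ASAP VAMC with a diagnosis other than ischemic stroke or TIA", followed by care outside a VAMC and known sleep apnea. Death is not among them. The Table 2 footnote in section 5.1.b, which explains a volume estimate, removes patients with "history of OSA, PSG in prior 5 years, death within 7-days of discharge, and hospice referral".

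**The concern.** Death before readmission is a competing event: once a patient has died, readmission cannot occur. A yes/no variable built from admissions alone gives that patient a no, which is the favourable value. The comparison between phases is then free of this problem only if death before readmission is equally common in both.

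The protocol gives reasons to doubt that. Section 1 links untreated sleep apnea to higher mortality, and Specific Aim 1 hypothesises a large fall in a composite that contains death. If some of that fall is in deaths, the added survivors can be readmitted and the apparent readmission benefit shrinks. If deaths rise instead, the readmission rate looks better than it should. The result also matters beyond Aim 1, because the business-case hypothesis in Aim 4 rests partly on avoided readmissions.

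**Working it through.** The protocol gives no power or sample-size calculation for readmission, so there is no figure of its own to reproduce. The check is of direction and size.

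**Inputs from the protocol (section 2, Specific Aim 1)**
- Hypothesised readmission: 33% control, 20% intervention, a difference of 13 points.
- Hypothesised 90-day vascular composite, which includes all-cause death: 10% control, 3.5% intervention. Under these hypotheses, post-discharge deaths within 90 days cannot exceed 10% and 3.5%.

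**Assumptions (not in the protocol)**
- d, the share of patients who die before any unplanned readmission, is varied.
- r, the readmission risk of the remaining patients, is held fixed while d changes. This also means that a patient whose death is averted has average readmission risk.

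**Formula.** With death scored as no readmission, observed rate = (1 − d) × r. The shift caused by mortality alone is r × (d before − d after).

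| r | d before → after | Observed before → after | Shift (points) |
|---|---|---|---|
| 33% | 2% → 1% | 32.34% → 32.67% | +0.33 |
| 33% | 5% → 2% | 31.35% → 32.34% | +0.99 |
| 33% | 10% → 3.5% | 29.70% → 31.85% | +2.1 |
| 33% | 3.5% → 10% | 31.85% → 29.70% | −2.1 |
| 20% | 2% → 1% | 19.6% → 19.8% | +0.2 |
| 20% | 5% → 2% | 19.0% → 19.6% | +0.6 |
| 20% | 10% → 3.5% | 18.0% → 19.3% | +1.3 |

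The 10% to 3.5% rows are extreme: every hypothesised composite event would have to be a death with no earlier readmission. At r = 33% the shift is 2.1 / 13 = 16% of the hypothesised effect.

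**Does it reverse the effect?** Take 33% and 20% as the risks among patients who do not die first, and apply the extreme mortality change as well. Control is 0.90 × 33% = 29.7% and intervention is 0.965 × 20% = 19.3%, a difference of 10.4 points. That is smaller than 13 but in the same direction. (The 2.6-point loss has two equal parts. Scoring 10% as non-events in both phases costs 0.10 × 13 = 1.3. The mortality change at r = 20% costs another 1.3.)

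**What a readmission-or-death measure would show.** If 33% and 20% are instead the observed rates, adding deaths without readmission gives 33 + 5 = 38% versus 20 + 2 = 22%, or in the extreme case 33 + 10 = 43% versus 20 + 3.5 = 23.5%.

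**The case against.** The strongest defence has four parts.

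- **The protocol nowhere says that deaths are scored as successes, and an unseen SAP could settle the matter.** This is true as far as it goes. But the protocol does not leave the outcome open: it writes out the numerator, the denominator exclusion and the model, and those rules together produce the result. It also deals with death for both neighbouring outcomes.
- **Readmission and the vascular composite measure different things, so treating death differently is no contradiction.** This stands. A utilisation rate is a legitimate outcome and fits the business case.
- **Deaths are already counted in the vascular composite, under the same model and data periods.** This largely stands. A mortality change would not go unseen. The composite does not show deaths separately, however, and does not correct a readmission result reported on its own.
- **Replacing readmission with readmission-or-death would change a named secondary outcome and overlap with the composite.** This stands, and the fix below does not replace it.

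Two stronger readings are tempting. A reader might infer that patients who die in the index stay are kept and counted as successes. The documents do not say so: readmission presupposes a discharge. Section 5.4 lists no death exclusion, and the Table 2 footnote concerns a volume estimate and names only death within 7 days of discharge. The point is simply unresolved. A reader might also put the distortion as high as 4 points (4 / 13 = 31% of the effect). That needs a 4-point change in death without readmission and certain readmission of every patient affected. Neither is in the documents.

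**Conclusion.** The point holds in a limited form. On the text as written, a death within 90 days of discharge without an unplanned readmission is a non-event in the readmission rate, and a mortality difference between phases moves that rate in the opposite direction. The missing time origin and the lack of an explicit rule for index-stay deaths are gaps in the definition, not evidence that such deaths are kept.

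The size is modest. For the smaller assumed mortality changes it is about 0.2 to 1.0 point. At the limit set by the protocol's own composite rates it is about 2.1 points, or 16% of 13, which dilutes the hypothesised effect without reversing it. These figures rest on assumed death rates and on averted deaths carrying average readmission risk; a higher risk would make the shift larger. Index-stay deaths, if kept, would come on top of the post-discharge bound. For a secondary outcome this is a cheap improvement worth making, not a threat to the trial's main conclusion.

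**What to change.** In the readmission paragraph of section 5.7.c:

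1. Define the denominator as patients discharged alive from the index stay and not transferred out.
2. Count the 90 days from discharge, as for the vascular outcome.
3. Keep 90-day all-cause readmission as the named secondary outcome.
4. Add a supportive analysis of unplanned readmission or death within 90 days of discharge, in the same mixed model and data periods.
5. Report the number and proportion of 90-day deaths by phase beside the readmission result.

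The cost is a few sentences, one recoded variable and one extra model. Vital status files are already listed as a data source in section 5.6. The supportive measure partly overlaps with the vascular composite. The 33% and 20% hypotheses can stay attached to readmission but should not be carried over to the supportive measure.

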## **Analysis of the Primary Effectiveness Outcome**

### **Diagnostic Rate Analysis**

A generalized linear mixed model will be fit to the patient-level outcome of diagnostic testing (yes/no) to conduct facility-level inference. The primary effect of interest is the effect of the intervention during active implementation versus baseline. Control sites are included to add accuracy in estimation of the secular time trend. A non-exact match approach is planned for this analysis (i.e., unconditional) since this model is being fit to patient-level data which will be used to conduct facility-level inference and there is no guarantee that patients in control sites that were loosely matched to an intervention site using facility factors are similar. This approach will use all available control site data without pairing specific control sites to each ASAP site. Effects in the model include a site-level indicator of intervention site vs control site, indicator for each site and data period corresponding to active implementation or sustainability phase, and time (as categorical, indicating each 7-month data period). The model will also include a random intercept for site to account for potential correlation among patients from the same site. Our interest is in testing the effect of the ASAP intervention on the proportion of patients who are diagnosed at the site-level. This model will also be fit adjusting for any important patient covariates (i.e., stroke severity). Both unadjusted and adjusted results will be reported. Contrasts from the model will also be estimated. All statistical tests will be two-sided, with p-values < 0.05 considered statistically significant. All analyses will include checking of assumptions and model fit.

**Analysis of Secondary Outcomes** As described above, because the treatment rate can only be assessed among the patients who have been diagnosed, we will be limited in our analysis of treatment. If several patients are diagnosed in the during the control phase (which is unlikely), we would use the same mixed model approach as with other outcomes. However, because we expect to have very

sparse data for the baseline phase, we plan to collapse data within each site across the baseline phases and the treatment phase and compare the within site treatment rates using a permutation test. Doing so will randomly flip the treatment labels of site-level treatment rates. Because there are 6 sites, there are  $2^6$  possible permutations of the treatment labels within pairs. The p-value will then be the proportion of permutations that lead to a test statistic at least as extreme as the actual data. Additionally, we will report the estimated site-level treatment rate during the baseline and intervention phases as well as the associated 95% CIs. We will also compare the overall treatment rate among all patients in the baseline phase to all patients in the active implementation phase using Fisher's exact test.

**90-day Recurrent Vascular Event Rate and Readmission Analysis** will be analyzed similarly to the primary outcome with the exception that the 7-month code-red data period (beginning 9/2021) will not be included. Models for the secondary outcomes (excluding treatment rate) will be fit without covariates (unadjusted) and additionally including patient-level factors (adjusted).

**Missing Data** Because we are using centralized chart review augmented by data from the CDW to collect our baseline characteristics and outcome data, we expect to have very little missing data. Only a few of the patient-level variables which may be included in the models adjusting for covariates may contain a small amount of missing such as stroke severity (as measured by the NIHSS). The amount of missing will be examined before deciding on the handling of missing data. Either complete-case or multiple-imputation will be used for models adjusting for patient-level factors. In the highly unlikely event that for a certain time period we are not able to get data from a specific site, the mixed effects model allows us to still use data for the other time periods for that site. The proposed mixed model methods are appropriate as long as data are missing completely at random (MCAR) or missing at random (MAR). If for any reason, we suspect the pattern of missing data is non-ignorable, more complex modeling approaches may be used.

**Specific Aim 1 Sensitivity Analyses** Given that implementation of ASAP may require some time after the kick-off we will examine intervention effectiveness if the intervention is considered starting in the second 7 months of the active implementation period. To do this, we will use the same generalized linear mixed model approach with the only difference being that sites will not be considered as being in the intervention phase until the second 7 months of the active implementation phase. A sensitivity analysis will also be conducted for the primary and secondary outcomes (except treatment rate) by including a time-varying, facility-level covariate for COVID-19 burden. Also, due to the Philips Respironics PAP machine recall, the national VA PAP recall level (green, yellow, red) was also collected. We plan to include all data periods for diagnostic testing for the primary analysis and remove the 7-month data period during which time the VA was in red status from analysis for all other outcomes, since theoretically patients could still be diagnosed even if treatment cannot be provided. However, since some sites did not even diagnose during the status red time, due to the ethical concerns of not being able to treat if the patient was found to have sleep

apnea, a sensitivity analysis will be examined where the 7-month code red period is removed also for the primary outcome. If feasible, we may explore the use of all data by including time-varying variables for VA PAP recall level (green, yellow, red) if the time-varying variable can be properly constructed for the 7-month time periods.

